### Study process

Potential participants will be identified from colonoscopy referrals according to site‐specific pathways and will usually be approached by telephone to assess interest and eligibility (to minimize face‐to‐face contact in the COVID‐19 era and increase convenience for patients). Inclusion and exclusion criteria are listed in Box 4. If interested and eligible, they will be sent an invitation letter, patient information sheet and consent form.

BOX 4COLO‐DETECT inclusion, exclusion and withdrawal criteriaInclusion criteria:
18 years of age or overable to give informed consentreferred for a colonoscopy for
clinical symptomssurveillance after previous colonoscopy or bowel pathologywithin the BCSPcolonoscopy is to be performed by a colonoscopist trained to perform GGC within the trial

Exclusion criteria:
absolute contraindications to colonoscopyconfirmed or expected pregnancyestablished or suspected large bowel obstruction or pseudo‐obstructioncurrent colorectal cancer or polyposis syndromeknown colonic stricture (meaning colonoscopy may be incomplete)known active colitis (e.g., ulcerative colitis, Crohn's colitis, diverticulitis, infective colitis)antiplatelet or anticoagulant therapy (except daily low‐dose [75 mg] aspirin) which has not been stopped for the procedure (precluding polypectomy)
Patients will also be excluded if they are undergoing any of the following:
inflammatory bowel disease surveillance procedureplanned therapeutic procedure or assessment of a known lesioncolonoscopy after referral for polyps identified on a Bowel Scope procedure (Bowel Scope was the national screening programme offering 55–59‐year‐olds a one‐off flexible sigmoidoscopy—it has ceased to be offered but some patients may have outstanding procedures that were delayed due to COVID‐19)
Patients in other research studies are not excluded from recruitment to COLO‐DETECT, other than where the colonoscopy is a follow‐up procedure in an interventional study examining prevention of adenoma or CRC recurrence.Withdrawal criteria:
withdrawal of consent to participate in the trial or for the colonoscopy at any point up to or during the procedurenew diagnosis of a polyposis syndromenew diagnosis of active colitis
For any participant who withdraws, data will be collected up to the point of withdrawal, and used.

Upon attending for colonoscopy, consent will be confirmed in writing and participants will complete the EQ‐5D‐5L health‐related quality of life questionnaire [40]. Participants will be randomized by recruiting staff 1:1 to GGC or SC [41] using a secure web‐based platform. Randomization will be stratified by age category (<60 years, between 60 and <74 years, ≥74 years), sex, study site and referral category (symptomatic or screening population). In the event of randomization platform unavailability, a coin toss will be used.

Standard colonoscopy represents standard care for colonoscopy at each study site. GGC incorporates all elements of SC and differs only in that the GI Genius™ will be turned on and activated for at least the whole of the inspection phase of withdrawal, although the investigators recommend to participating colonoscopists that the GI Genius™ is activated prior to the procedure. Procedural data will be recorded onto a Case Report Form (CRF). Post‐procedure, participants in both arms will undergo standard post‐colonoscopy care and discharge procedures for each site.

Prior to discharge participants will be given a patient experience questionnaire (the validated Newcastle ENDOPREM™ [37]) and a second iteration of the EQ‐5D‐5L to complete and return in a pre‐paid envelope. Follow‐up will cease upon completion of a post‐procedure review between days 14 and 21. This may include accessing medical records (including endoscopy reports and histology) and a telephone call to assess whether any adverse events (AEs) or serious adverse events (SAEs) have occurred. No further contact will be required for study participation, although participants will be asked to consent to long‐term (up to 5 years) passive follow‐up of health outcomes through endoscopy data, medical records and national databases such as the National Cancer Registry Database, Hospital Episode Statistics data, National Endoscopy Database [42] and link to the CORECT‐R data repository [43]. Where data are currently anonymized participant consent will be sought to link data when this becomes possible. Present and future clinical care will be unaffected by study participation.

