### Data collection

Baseline data (age, sex, indication for colonoscopy, colonoscopist study ID and BCSP accreditation status) will be recorded into a CRF pre‐procedure along with trial arm. Post‐procedure, the following data will be recorded:
medications usedvideo processor manufactureruse of a mucosal visualization deviceprocedure timings (start/end times, withdrawal commencement and withdrawal time—in minutes)furthest extent reached (and reason caecum not reached, if relevant)whether retroflexion was performedquality of bowel preparation (using standard JAG classifications)nurse‐assessed and colonoscopist‐assessed patient comfort scores (using the modified Gloucester comfort score)pathology identified (including polyps, cancer, inflammatory bowel disease etc.)whether any polyps were detected on insertion or withdrawalpolyp location, size, morphology, removal method and retrieval statushistology of any biopsies or polyps retrievedoccurrence of any AEs or SAEsanticipated interval to any subsequent surveillance colonoscopy (based solely on the application of the latest British Society for Gastroenterology guidelines [38] to recorded endoscopic findings and histology)whether GI Genius™ was deactivated or suffered a technical malfunction during the colonoscopy (relevant for planned process evaluation)

If required, participants will receive the following: a verbal reminder (by telephone) from a member of the research team to complete and return their post‐procedure questionnaires; with a written reminder (and another copy of the questionnaire) sent 4 weeks post‐procedure.

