### Adverse events

Adverse events (any new medical occurrence or worsening of an existing condition) will be monitored from the date of colonoscopy until cessation of follow‐up or withdrawal from the study (whichever occurs first) and will be recorded on medical notes and CRFs.

Serious adverse events will be managed clinically as per normal procedures. They will be recorded on a bespoke form and reported to the sponsor as soon as the local research team becomes aware of the SAE, in line with current good clinical practice guidance [44]. SAEs must be reported to the sponsor even if they are considered by the local site team and Principal Investigator to be expected, or unrelated to the colonoscopy. If the sponsor deems it necessary, they will be reported to the NHS Research Ethics Committee (REC) within 15 days. Standard NHS complaints procedures and indemnity arrangements are in place to support participants who have been harmed during study participation.

GI Genius™‐assisted colonoscopy is not known to entail any additional risks to participants. The exception would be that, if more polyps are identified during GGC than SC, then assessing and managing these may result in an increase in procedure duration (provisional estimate of 5% additional time), which may affect patient comfort; and if additional polypectomies are performed then the overall risk of complications (mainly bleeding, perforation) may be increased. Universally accepted best practice in colonoscopy remains that all polyps (except rectal hyperplastic polyps) should be excised, assuming that the marginally increased risk of complications does not outweigh the potential benefit of reduced future CRC risk. Accordingly, AEs will be monitored to determine whether any increase in detection leads to more polypectomies and whether this correlates with an increased AE rate, including bleeding and perforation as well as sedation‐related risks. This will be critical for informing the planned economic evaluation.

All AEs and SAEs will be reported to and discussed with an independent Data Monitoring Committee (DMC). The Chair of the DMC will ask for review of all AEs and SAEs and an opinion will be given regarding whether they are related to the study. The results of discussions with and by the DMC will be presented to the independent Trial Steering Committee (TSC).

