Analyses will be performed using a 5% significance level (two‐sided) and effect size estimates will be presented with 95% confidence intervals. All analyses will be completed on an intention‐to‐treat and per protocol basis and will include all randomized patients. We will additionally undertake sensitivity analysis limiting analysis to patients with complete colonoscopy. Should substantial data be found to be missing for a measure or variable (i.e., ≥5%), predictors of missingness will be investigated using regression modelling. Multiple imputation may also be employed to address missing values where appropriate.

A ‘within study’ economic evaluation will be conducted to determine cost effectiveness of GGC versus SC from the perspective of the NHS. It will be based upon the costs of randomized interventions received and on use of subsequent care and services. Use of resources will be collected including duration of procedure, resource use and associated staff costs (including grade of staff), any additional treatment prescribed (e.g., analgesics), appointments missed, any hospital inpatient stays, and any AEs and associated treatment. The EQ‐5D‐5L will provide utility information. Incremental cost effectiveness ratio (cost per quality‐adjusted life‐year) will be estimated with robustness of results evaluated in a sensitivity analysis. The incremental cost effectiveness ratio will be compared against thresholds used to establish value for money in the NHS (currently in the region of £20 000–£30 000 per quality‐adjusted life‐year).

Economic modelling approaches will be used to explore longer‐term economic consequences and patient benefits (including effects on CRC) of GI Genius™, across a lifetime horizon.

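### Box 4 turns a request to stop the colonoscopy into withdrawal from the trial, which cuts off patient-reported and safety follow-up for procedures that were probably among the least tolerable

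*Protocol article*

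**What the plan says.** In the protocol article, Study process, Box 4 gives as the first withdrawal criterion "withdrawal of consent to participate in the trial or for the colonoscopy at any point up to or during the" procedure. It closes with "For any participant who withdraws, data will be collected up to the point of withdrawal, and used".

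The same section places the ENDOPREM questionnaire and the second EQ-5D-5L after the procedure, handed over before the participant goes home and returned by post. The final review falls between days 14 and 21.

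Data collection opens its main list with "Post‐procedure, the following data will be recorded". The list includes "furthest extent reached (and reason caecum not reached, if relevant"), nurse- and colonoscopist-assessed "patient comfort scores (using the modified Gloucester comfort score"), polyp details, histology and adverse events.

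Adverse events says monitoring runs from the day of colonoscopy until follow-up ends or the participant leaves the study, whichever is earlier. It also notes that finding more polyps with GGC may lengthen the procedure, "which may affect patient comfort; and if additional polypectomies are performed then the overall risk of complications" may rise.

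Data analysis states that all analyses are by intention to treat and per protocol "and will include all randomized patients", with an additional "sensitivity analysis limiting analysis to patients with complete colonoscopy".

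**The concern.** Two different events share one criterion. One participant no longer wishes to be in the study. Another is content to be in the study but asks for the procedure to end, for example because of pain. The second has withdrawn consent for the colonoscopy only, yet Box 4 handles both alike and ends data collection at that moment.

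This matters because poor tolerance is a plausible main reason for asking to stop, and tolerance is part of what the trial measures. Patient experience is a listed secondary objective, EQ-5D-5L supplies the utilities for the economic evaluation, and the adverse event comparison is described as critical to that evaluation. If the participants with the worst procedures are the ones without these data, the levels look too favourable. If they are more frequent in one arm, the contrast is distorted as well.

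**Working it through.** **Step 1. What falls before and after the stop.** Suppose a participant asks to stop part-way through.

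| Item | When it arises | Position under Box 4 |
|---|---|---|
| Furthest extent, reason caecum not reached | Fixed at the stop | Known up to withdrawal, so usable |
| Polyps seen or removed | Before the stop | Usable |
| Histology of polyps already removed | Result comes later | Unclear |
| Staff comfort scores | Observed before the stop, written down afterwards | Unclear |
| ENDOPREM, second EQ-5D-5L | After the procedure | Not due |
| Day 14–21 review | After the procedure | Not due |
| Adverse event monitoring | From the day of colonoscopy onward | Ends at withdrawal |

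The three not-due or ended rows follow from the text. The two unclear rows depend on how a site reads the instruction.

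**Step 2. Can the analysis recover the loss?** Analysing all randomized patients keeps these people in the denominator but cannot supply questionnaires or adverse event data that were never sought. Data analysis makes multiple imputation optional and investigates predictors of missingness only when at least 5% of a measure is missing.

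**Step 3. Does the plan's own sample size change?** It reproduces. With 27.6% versus 34.6%, two-sided alpha 0.05 and 90% power, using unpooled variance:

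n per arm = (1.960 + 1.282)² × (0.276×0.724 + 0.346×0.654) / 0.07² = 913.7, so 914 per arm and 1828 in total. Then 1828 / 0.90 = 2031.1, so 2032. The point does not alter this.

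**Step 4. How many participants?** The documents do not give the share of procedures stopped on request. The only related figure is the 10% allowance for incomplete colonoscopies. I assume a share s of the incomplete procedures is stopped on request: number = 2032 × (incomplete rate) × s.

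| Incomplete (10% in plan, 5% assumed) | s = 10% | s = 25% | s = 50% |
|---|---|---|---|
| 5% | 10 (0.5%) | 25 (1.3%) | 51 (2.5%) |
| 10% | 20 (1.0%) | 51 (2.5%) | 102 (5.0%) |

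Only the most extreme cell reaches the 5% trigger on its own.

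**Step 5. What could selective loss do?** This is an illustration with assumed rates: 2% of SC and 3% of GGC participants stop because of discomfort and would all report severe discomfort; 5% of the remainder do so in both arms.

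- All followed: SC 0.98×0.05 + 0.02 = 6.9%; GGC 0.97×0.05 + 0.03 = 7.85%; difference 0.95 percentage points.
- Stopped procedures lost: 5% versus 5%; difference 0.
- Equal stopping at 2.5% in both arms: 0.975×0.05 + 0.025 = 7.4% in each if followed, 5% in each if lost; difference 0 either way.

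The levels are too low in every case. The contrast is distorted only when stopping differs by arm.

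**The case against.** The strongest reply is that Box 4 explicitly keeps and uses data up to withdrawal, all randomized patients are analysed, and restriction to complete colonoscopies is only a sensitivity analysis. The post-procedure instruction governs when the form is filled in, not when the facts arise. All of this stands, and it disposes of three stronger readings that a reader might draw:

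- That stopped procedures vanish from caecal intubation. Extent is known at the stop, there is a field for it, and no section removes these participants.
- That a participant cannot be both a withdrawal and an incomplete colonoscopy. The article never says the two are exclusive.
- That polyps already found are dropped from MAP and ADR. Nothing says so; at most the handling of later histology is ambiguous.

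A second reply is that an arm difference is speculative. The extra time expected with GGC comes from managing extra polyps, and the device must be active only during withdrawal of the scope, whereas a stop short of the caecum happens on insertion. This weakens the mechanism without removing it: activation before the procedure is recommended, and stops can also occur on withdrawal of the scope.

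A third reply is that this is a condensed article, and the full protocol and Data Management Plan may grade withdrawal by type. They may. But the point does not rest on an omission: the article states a rule, and that rule merges the two consents.

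**Conclusion.** The point holds in limited form. As written, Box 4 ends ENDOPREM, the second EQ-5D-5L, the day 14–21 review and adverse event monitoring for a participant who withdraws consent only for the colonoscopy, and leaves comfort scores and pending histology to site interpretation. That loss is probably related to tolerance, and the analysis population cannot repair it.

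Its size is unknown. The range of about 0.5% to 5% of participants rests on assumed stopping shares, and the vanishing difference in the illustration rests on assumed unequal stopping rates and on every stopped participant having severe discomfort. With equal stopping rates the contrast would not be biased, although the levels would be. The effect is on secondary, safety and economic data. Harm to caecal intubation, MAP, ADR or the sample size is not shown. The change is still worth making, because data not collected cannot be recovered at the analysis stage.

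**What to change.** Limit the trial-withdrawal criterion in Box 4 to withdrawal of consent to take part in the trial or to provide data. Add that a participant who withdraws consent only for the colonoscopy after scope insertion stays in the trial as an incomplete colonoscopy. For that participant, complete the CRF (extent reached, reason for stopping, comfort scores, polyps and histology), ENDOPREM, EQ-5D-5L, the day 14–21 review and adverse event monitoring, unless the participant also declines these. Score caecal intubation on the extent actually reached.

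The cost is a short rewording of Box 4 and a note to sites. There are no new assessments, and the decision to stop the procedure is untouched. The downside is that sites must ask which consent is being withdrawn, at what may be an awkward moment; the question can wait until after the procedure has ended.

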### Colonoscopists and training with GI Genius™

Every colonoscopist at participating sites will be eligible to participate. Participating colonoscopists will undergo standardized training in how to use the GI Genius™ and to deliver SC and GGC according to study protocol, after which they will be required to perform a set number of GGC procedures prior to participating. No testing will be conducted unless requested by the colonoscopist. Colonoscopists who perform colonoscopy within the BCSP undergo additional accreditation and so may be considered to represent expert practice [15], meaning that over‐representation of BCSP‐accredited colonoscopists may not reflect routine clinical practice in the UK. A range of experience amongst participating colonoscopists is anticipated and desirable; to facilitate subgroup analysis by colonoscopist experience, it will be assessed by BCSP accreditation status, lifetime procedure numbers and yearly procedure numbers for the last 3 years (Figure 3).

**FIGURE 3 codi16219-fig-0003:**
[figure not shown]
COLO‐DETECT participant flowchart

### Sample size

The primary outcome for COLO‐DETECT is the difference in MAP between GGC and SC (for which a clinically meaningful mean difference has been considered to be 0.50 for screening patients and 0.30 for symptomatic patients) (based on communications between the senior author, the clinicians involved in the trial and taking opinion from other experts). Due to the importance of ADR in detection studies and its historical widespread use it is important that this study is also powered to demonstrate a difference in ADR.

Exploratory—and, importantly, separate—sample size calculations for MAP and ADR indicate that a larger sample would be required to detect a significant difference in ADR than in MAP; COLO‐DETECT has therefore been powered to detect a clinically meaningful and statistically significant difference in ADR, which exceeds that required to detect such a difference in MAP. This represents a difference of 7% in ADR (with a clinically meaningful difference deemed to be 10% for screening patients and 5% for symptomatic patients). Assuming a mixed sample of 40% screening (BCSP) patients and 60% symptomatic patients, with a baseline ADR of 27.6% across the sample (by aggregating BCSP and non‐BCSP data), a superiority design including 2032 participants will be required to provide 90% power for a two‐sided test for difference in proportions with an alpha value of 0.05. Allowing for 10% attrition due to incomplete colonoscopies, the target sample size will be 1828 participants having a complete colonoscopy. This sample size will more than enable detection of a pooled difference of 0.18 mean difference in MAP.

### Data collection

Baseline data (age, sex, indication for colonoscopy, colonoscopist study ID and BCSP accreditation status) will be recorded into a CRF pre‐procedure along with trial arm. Post‐procedure, the following data will be recorded:
medications usedvideo processor manufactureruse of a mucosal visualization deviceprocedure timings (start/end times, withdrawal commencement and withdrawal time—in minutes)furthest extent reached (and reason caecum not reached, if relevant)whether retroflexion was performedquality of bowel preparation (using standard JAG classifications)nurse‐assessed and colonoscopist‐assessed patient comfort scores (using the modified Gloucester comfort score)pathology identified (including polyps, cancer, inflammatory bowel disease etc.)whether any polyps were detected on insertion or withdrawalpolyp location, size, morphology, removal method and retrieval statushistology of any biopsies or polyps retrievedoccurrence of any AEs or SAEsanticipated interval to any subsequent surveillance colonoscopy (based solely on the application of the latest British Society for Gastroenterology guidelines [38] to recorded endoscopic findings and histology)whether GI Genius™ was deactivated or suffered a technical malfunction during the colonoscopy (relevant for planned process evaluation)

If required, participants will receive the following: a verbal reminder (by telephone) from a member of the research team to complete and return their post‐procedure questionnaires; with a written reminder (and another copy of the questionnaire) sent 4 weeks post‐procedure.

### Adverse events

Adverse events (any new medical occurrence or worsening of an existing condition) will be monitored from the date of colonoscopy until cessation of follow‐up or withdrawal from the study (whichever occurs first) and will be recorded on medical notes and CRFs.

Serious adverse events will be managed clinically as per normal procedures. They will be recorded on a bespoke form and reported to the sponsor as soon as the local research team becomes aware of the SAE, in line with current good clinical practice guidance [44]. SAEs must be reported to the sponsor even if they are considered by the local site team and Principal Investigator to be expected, or unrelated to the colonoscopy. If the sponsor deems it necessary, they will be reported to the NHS Research Ethics Committee (REC) within 15 days. Standard NHS complaints procedures and indemnity arrangements are in place to support participants who have been harmed during study participation.

GI Genius™‐assisted colonoscopy is not known to entail any additional risks to participants. The exception would be that, if more polyps are identified during GGC than SC, then assessing and managing these may result in an increase in procedure duration (provisional estimate of 5% additional time), which may affect patient comfort; and if additional polypectomies are performed then the overall risk of complications (mainly bleeding, perforation) may be increased. Universally accepted best practice in colonoscopy remains that all polyps (except rectal hyperplastic polyps) should be excised, assuming that the marginally increased risk of complications does not outweigh the potential benefit of reduced future CRC risk. Accordingly, AEs will be monitored to determine whether any increase in detection leads to more polypectomies and whether this correlates with an increased AE rate, including bleeding and perforation as well as sedation‐related risks. This will be critical for informing the planned economic evaluation.

All AEs and SAEs will be reported to and discussed with an independent Data Monitoring Committee (DMC). The Chair of the DMC will ask for review of all AEs and SAEs and an opinion will be given regarding whether they are related to the study. The results of discussions with and by the DMC will be presented to the independent Trial Steering Committee (TSC).

